### Outcomes

The primary endpoint is resting-state EEG, and the secondary endpoints are sleep quality, quality of life, and migraine pain level. The Confounders will be the level of migraine pain (Russo et al., 2018), gender (Victor et al., 2010) (Kelman, 2006), and age (Echiverri et al., 2018), COVID-19 (Haghdoost et al., 2021).

The migraine pain level questionnaire that records the general health condition of the participants and the characteristics of migraine which including, frequency, severity, and duration will be included. Level of pain scored on a four-point numerical rating scale (0–3) equivalent to no, mild, moderate, and severe pain [36]: 0 no pain. 1 mild pain, does not interfere with usual activities 2 moderate pain, inhibits but does not wholly prevent usual activities 3 severe pain, prevents all activities. The other components are expressed as either decreased/ increased/ remains the same/ unable to recall.

Pittsburgh Sleep Index is a self-rated questionnaire that assesses sleep quality and disturbances over a 1-month interval. 19 individual items generate seven component scores: subjective sleep quality, sleep latency, duration, habitual sleep efficiency, sleep disturbances, use of sleeping medication, and daytime dysfunction. The sum of scores for these seven components yields one global score. The sleep component scores are summed to yield a total score ranging from 0 to 21, with the higher total score (referred to as global score) indicating worse sleep quality [37].

Migraine Specific Quality of life is a 14-item instrument that measures the impact of migraine across three essential aspects of a patient’s health-related quality of life over the past 4 weeks: role function-restrictive (RR), role function-preventive (RP), and emotional function (EF). Raw dimension scores are computed as a sum of item response and rescaled from a 0 to 100 scale. The higher the score better is the quality of life [38].

Recording of resting-state EEG will be performed using MUSE 2 a portable EEG recording device. The headset has four dry sensors (two mastoid and two forehead sensors). It fits over the ears and extends at an angle over the middle of the forehead when properly fitted with 3 reference electrodes. Once the headband is fitted, as shown in Fig 2b, the mind monitor app will be used for data acquisition. There will be horse to represent the sensors on the Muse and its connection. Solid ovals indicate a good connection, outlines indicate a poor connection and an empty space indicates no connection. The data acquisition space will be 100–200 cm from the computer/ tablet monitor displaying the stimulus presentation sequence. In the mind monitor application, the presentation of brain wave sequence can be in absolute, raw, discrete, accelerometer, and spectrogram views. In this study, raw EEG presentation values will be used for stimulus presentation sequence. So, each sensor’s raw data will be recorded in microvolts (μV). The sensors will be TP9 (left ear), AF7 (left forehead), AF8 (right forehead), TP10 (right ear), AUXR (right auxillay). The participant will be instructed not to clench teeth and blink eyes often since it can alter the activity recorded. The resting-state EEG will be recorded for a total of 20 minutes alternating between eyes open and eyes closed condition [39–41]. Details of the SPIRIT enrollment and the experimental protocol are as illustrated in Figs 1 and 2.

**Fig 1 pone.0291534.g001:**
[figure not shown]
SPIRIT schedule of enrollment, interventions, and assessments.

**Fig 2 pone.0291534.g002:**
[figure not shown]
Protocol of resting-state EEG recording. a- MUSE 2 electrodes location, b- MUSE 2 setup, c- EEG recording from Mind Monitor App.

### Procedure and stages

Fig 3(a) and 3(b) summarizes the consort diagram and overview of the procedure to explain the study planned.

**Fig 3 pone.0291534.g003:**
[figure not shown]
(a): Study protocol (b): OverView of study protocol.

Volunteer of undergraduate and postgraduate students will be recruited as participants, and a questionnaire will be distributed to confirm the migraine symptoms among students in UTAR Sungai Long campus using Migraine Screen and ICHD 3 Questionnaires additionally, these participants will be assessed for exclusion criteria. Once confirmed with migraine symptoms, the level of disability using the Migraine Disability Assessment Scale questionnaire (MIDAS) will be assessed. The subjects in MIDAS I-IV will be randomly allocated to Group I: Aerobic training, Group II: Biofeedback training, Group III: placebo group.

The physiotherapy intervention phase will be initiated. The pre-test outcome measures will be assessed using 4-point pain intensity scale, the Pittsburgh Sleep Quality Index, Migraine Specific Quality of Life questionnaires, and recording of resting-state EEG using the MUSE 2 instrument. On the first day of the study, participants’ migraine phases will be designated as inter-ictal, pre-ictal, ictal, or post-ictal based on the subjective questions. The ictal phase will be coded when the participant suffered a migraine attack on the day session. Pre-ictal and post-ictal phases will be coded when the migraine is within 36 h before or after an ictal phase. The inter-ictal phase will be coded in a pain-free period between the pre-ictal and post-ictal phases. During this intervention phase, the subjects in all groups will be requested to maintain a headache diary based on the national headache foundation [42]. The headache diary consists of date of migraine symptom, start time and end time of migraine, intensity (1–10 most severe being 10), preceding symptoms, medication (and dosage), relief of symptoms (complete/ moderate/ none), any other related activities/ exercises, supplements take, and other symptoms occurred (chest pain, shortness of breath, leg cramps/ fatigues). The outcome measures will be measured at baseline and at the end of the intervention at the 6^th^ week.

After 6 weeks of intervention, recording resting-state EEG, migraine pain level, sleep quality using Pittsburgh sleep quality index and QoL using Migraine specific quality of life will be assessed and subjected to analyses.

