## Methodology

This study is a pilot randomized control trial with a pre-and post-test design that focuses on the preliminary efficacy of aerobic training among university students with migraine symptoms. The primary endpoint is resting-state electroencephalography (EEG). The secondary endpoints are sleep quality, quality of life, and migraine pain level. This study will be conducted at Physiotherapy Center, Universiti Tunku Abdul Rahman, Sungai Long Campus. The outcome measures will be performed at baseline and end of intervention (6^th^ week) to compare the data obtained. The study is approved by UTAR Scientific and Ethical Review Committee (U/SERC/188/2022). The informed consent form will be signed and dated before the start of the actual intervention. Parallel assignment intervention model will be used. The study is also registered with ClinicalTrials.gov Protocol Registration and Results System (Identifier: NCT05741775).

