### Randomization

A simple random sampling method will be employed as the sampling technique in recruiting the subjects. Upon successful recruitment of participants, and with Migraine Disability Assessment Scale (MIDAS) Questionnaire, the subjects will be allocated into either of the three groups (Group 1: aerobic training, Group 2: biofeedback training, Group 3: placebo group). The subjects will be given a random number in an excel sheet and ranked. Following ranking, the ranked participant will be divided by size and group accordingly.

Simultaneously using MIDAS, each group will have 7–10 participants depending on each level of disability on MIDAS. In the Migraine Disability Assessment Scale (MIDAS) Questionnaire that assesses headache-related disability, the respondents are required to answer five questions. The number of days in each question will be summed up and the scoring indicates the activity limitation due to migraine in the past 3 months. The participants are then categorized into no or little disability (0–5), mild disability (6–10), moderate disability (11–20), and severe disability (21+) (Stewart et al., 2001).

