### Blinding

A single blinding method will be used. The outcome assessor will be blinded. The outcome assessor will not know whether participants are from aerobic training, biofeedback training or placebo group. Single blinding will be used in this study because the results are less likely to be biased.

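### The readable procedure text puts the pre-test measures after random allocation of unblinded participants, so self-reported baselines could be influenced by the arm

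*Protocol article*

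**What the plan says.** The order of steps is told in the protocol article under Procedure and stages, in the text that follows Fig 3. Volunteers are screened with the migraine questionnaires, and "additionally, these participants will be assessed for exclusion criteria". MIDAS is then scored. Next comes allocation: "The subjects in MIDAS I-IV will be randomly allocated to Group I: Aerobic training, Group II: Biofeedback training, Group III: placebo group". A new paragraph opens with "The physiotherapy intervention phase will be initiated. The pre-test outcome measures will be assessed using 4-point pain intensity scale" and goes on to the sleep and quality-of-life questionnaires and the EEG recording. The coding of migraine phase from subjective questions comes after that.

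The Randomization section has the same trigger for allocation: "Upon successful recruitment of participants, and with Migraine Disability Assessment Scale (MIDAS) Questionnaire, the subjects will be allocated into either of the three groups". It does not require that baseline outcomes have been measured.

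Methodology says only "The outcome measures will be performed at baseline and end of intervention (6^th^ week) to compare the data obtained" and does not place baseline before or after allocation. On consent it says "The informed consent form will be signed and dated before the start of the actual intervention". Blinding says "A single blinding method will be used. The outcome assessor will be blinded". The Statistical analyses section plans a mixed design analysis and an intention-to-treat analysis.

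**The concern.** A baseline is safe to use in a treatment comparison because it is recorded before anyone can react to the assignment. Here the arms are supervised exercise, EMG biofeedback and an education sheet, so a participant who has been told the assignment cannot mistake it. Pain level, sleep quality and migraine-specific quality of life are all answered by the participant, and blinding the assessor does not protect them. Someone who hoped for exercise and received a leaflet, or the reverse, may answer the pre-test differently for that reason.

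Two things are at stake. First, the design compares pre with post, so a baseline difference caused by the arm becomes part of the estimated effect. Outcomes also lists migraine pain level as a confounder. If the pre-test pain score serves as that covariate, the adjustment would use a variable that the arm may have affected. Second, a person who withdraws after learning the arm and before the pre-test has been randomised but has neither a baseline nor a week-6 value. The intention-to-treat analysis would then rest on assumptions alone for that person.

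**Working it through.** The plan gives no figure on this point, so the check is mainly a reading of the sections side by side.

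1. **Order of steps.** Procedure and stages: screening and exclusion, MIDAS, allocation, intervention phase begun, pre-test. Randomization: recruitment and MIDAS, then allocation. The Abstract also bases assignment on the disability questionnaire. Methodology: baseline and week 6, not placed relative to allocation. No readable section puts the pre-test before allocation.

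2. **Who could know the arm.** Blinding covers the outcome assessor only. No section says when participants are told their arm, and none provides for withholding it until the pre-test is done.

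3. **Which outcomes are exposed.** Of the four outcomes, three are self-reported (pain, sleep, quality of life), and all three are secondary. The primary outcome, resting-state EEG, is recorded by a device under a blinded assessor.

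4. **How a shift would pass through.** Let δ be the between-arm difference in reported baseline caused by knowing the arm, and τ the true difference at week 6. Assume that the week-6 answers are not altered by δ.
   - Difference in change scores (group by time): expected value τ − δ, so the bias is −δ, the whole shift.
   - Baseline-adjusted analysis with slope b on baseline: τ − bδ, so the bias is −bδ.
   - Group effect averaged over the two occasions: (τ + δ)/2 instead of τ/2, so the bias is +δ/2.

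   All three use the baseline and all three are affected. The sign of δ is not known.

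5. **Sample size.** With f = 0.4, 3 groups, 4 measurements, alpha 0.05, power 0.95 and an assumed correlation of 0.5 between measurements (the article gives none), the noncentral F calculation gives N = 66 with power 0.958. Then 66/(1 − 0.25) = 88. Both stated figures reproduce, and the present point changes neither.

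**The case against.** The strongest reply is that the procedure text is a loose narrative and not a timetable. It mentions the first day of the study only after allocation and the pre-test, so sentence order cannot be taken literally throughout. The schedule proper belongs to Fig 1 (SPIRIT schedule) and Fig 3 (study flow), which are not shown and may put baseline first. This limits certainty. It does not supply the opposite order, and the Randomization section agrees with the narrative. If the figures differ, the text still has to be brought into line with them.

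Second, generating an allocation by ranking random numbers in a spreadsheet does not disclose it. That is correct, and the bias in the self-reports depends on disclosure before the pre-test.

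Third, the sleep questionnaire covers one month and the quality-of-life questionnaire four weeks, so the period asked about lies largely before allocation. This limits reporting bias but does not remove it, since the answers are still given after allocation.

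Two stronger readings are tempting, and neither is supported:

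- A reader might infer that consent follows allocation, so that entry to the trial depends on the arm. The consent sentence sets only a latest time and is compatible with consent before randomisation. Unwillingness to take part is also an exclusion criterion, and exclusions are checked before allocation.
- A reader might size the bias by assuming a shift of 0.1 to 0.3 SD and dividing by the largest pairwise difference implied by f = 0.4 with three groups: 0.4 × 6/√8 = 0.85 SD to 0.4 × √6 = 0.98 SD, hence 0.1/0.98 = 10% to 0.3/0.85 = 35%. The shift has no source in the documents. The f is specified for a between-factors effect, whereas the bias in question falls on a pre/post contrast. The percentage should not be used.

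**Conclusion.** The point holds as a defect in the stated order. As written, the pre-test follows allocation and the start of the intervention phase, in a trial whose participants are not blinded. If that order is followed and participants know their arm, the self-reported secondary baselines can be biased and the bias enters the pre/post comparison. Early leavers would have no outcome data. The primary EEG is less exposed to reporting bias, though it too would be missing for someone who leaves before the pre-test.

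Neither the size nor the direction of the bias can be derived from the documents. The conclusion rests on two conditions that the readable text leaves open: that the arm is disclosed before the pre-test, and that Figs 1 and 3 do not show another order. The correction should be made all the same, because it concerns an order that the text states and it costs little. Nothing in the article shows that consent is taken after allocation.

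**What to change.** Re-order Procedure and stages so that eligibility, MIDAS and every pre-test measure (pain, sleep, quality of life, EEG and migraine-phase coding) are completed before allocation is made, or at least before it is disclosed to the participant. Place the start of the intervention phase after that. Add to Randomization that allocation requires a completed pre-test, and check that Figs 1 and 3 show the same order.

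As a wording clarification only, Methodology should say that consent is signed before randomisation.

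The steps are already planned, so the change is mainly one of order. The possible downside is timing. If a recruited list is ranked and split in batches, people tested early may wait longer between baseline and the start of treatment, since each EEG recording alone takes 20 minutes. Keeping the order of testing and allocation but withholding the assignment until each person's pre-test is done would avoid most of that wait.

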### Protocol

#### Aerobic training

Participants in the aerobic group will undergo training that includes neck exercise, static bicycle, and walking. The participants start the session with a warm-up for 5 minutes followed by 30 minutes of aerobic exercise and end with 5 minutes of cool-down exercise. 40 minutes/ session, 3 times per week for 6 weeks. Fig 4 summarizes the exercise protocol involved in the aerobic training group.

**Fig 4 pone.0291534.g004:**
[figure not shown]
Protocol of aerobic training. a- Neck exercise with resistance band, b- Static bicycle, c- Treadmill.

The warm-up exercise will include light aerobic activity and some dynamic stretching movements. The exercises included will be fast-paced side steeping, jogging on the spot, arm swings, lunges, and squats, exercise to be performed for 10 repetition, each* 3 sets/ 1 minute each [43]. Similarly, the cool-down exercises will include buttock stretch, hamstring stretch, inner thigh stretch, calf stretch, and thigh stretch. Each stretch to be performed for 5 repetitions with a hold time of 15 seconds for each [44]. Fig 5 summarizes the warm-up and cool-down exercises.

**Fig 5 pone.0291534.g005:**
[figure not shown]
Warm up and cool down exercise.

During the exercise, the subjective measure of how hard the participant feels during the activity is measured using Borg’s Rating of Perceived Exertion (RPE) [45,46].

Similarly, during aerobic training, the exercise intensity will correlate with how hard the activity feels. The objective measurement of exercise intensity using heart rate calculation method will be used in this study. To calculate the heart rate, the Karvonen method, otherwise called as heart rate reserve (HRR) formula, takes the resting heart rate into consideration by introducing the difference between maximum heart rate and resting heart rate. Using the Karvonen principle, the target heart rate will be calculated using the formula: [(max HR − resting HR) × %Intensity] + resting HR. The maximum heart rate (max HR) will be calculated using the formula: 220-age. The resting heart rate (resting HR) will be calculated by measuring pulse at rest. For moderate-intensity physical activity, the target heart rate should be between 64% and 76% of the maximum heart rate [47].

An elastic band secured around the head will apply local pressure over the area. Red color bands will be used since the target area is muscle around the chin or shoulder. This strengthening exercise will use a dynamic isometric thera-band exercise that will be performed in a sitting position with a single series/ set of 15 repetitions in forward, obliquely toward the right and left, and backward.

Kettler Computeranleitung Advanced display will be used to train static cycling. Upon starting the machine, a new user item will be created, and the desired heart rate will be entered. During training, the participant grips the detector and starts cycling, Borg’s RPE will be maintained at 11–14. The central graphic in the display shows whether the participant is within range or whether above or below the target range. The average exercise bike pedaling speed will be 50 to 60 rpm.

ProAction BH Treadmill G6700 instrument will be used for aerobic training. Following the target heart rate calculation, the participant will start to walk at a comfortable pace by griping the detector, and Borg’s Rating of Perceived Exertion (RPE) measures the physical activity intensity level will be maintained at 11–14, and the speed of walking will be at 4 mph and depending on RPE response the speed will be either be maintained or increased to 5 mph.

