Habitual aerobic exercise has a major advantage of preventing or reducing symptoms of several chronic diseases and medical conditions [21]. Aerobic or cardiovascular exercise is a form of bodily movement fueled by aerobic energy-generating processes, where the energy demands of the exercise do not exceed the rate at which the cardiovascular system can supply oxygen to working muscles [22]. Aerobic exercises have already been proven to reduce the frequency, duration, severity or associated disability in migraine [21]. The physiology is that when one exercise, the body releases endorphins, the body’s natural painkillers and natural anti-depressants chemicals called enkephalins. According to Centre of Disease Control and Prevention (CDC), adults should exercise 150 minutes of moderate-intensity aerobic exercise and two or more days a week of muscle strengthening each week to relieve migraine or primary headaches. Similarly, a study comparing neck treatment and aerobic exercise concluded that five weeks of intervention for migraine patients responded with better outcomes [23]. According to the American migraine foundation, the exercise program should include cardiorespiratory fitness, flexibility exercises, and muscular strengthening. For migraines, mild to moderate aerobic exercise is highly recommended. But most of the studies’ primary outcome is only pain intensity, severity, duration, and frequency. Recent research found that the resting state brain waves were altered during the neuroimaging [24], and that the spatio-temporal dynamics exist in migraine patients during the resting-state. Moreover, the temporal dynamics, spatial changes, and clinical traits such as migraine disability interact [25], indicating the need for further analysis and appropriate treatment strategies. Hence this study aims to assess the preliminary effects of aerobic training on migraine pain level, sleep quality, quality of life, and resting-state brain waves compared with EMG biofeedback training and placebo group.

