### Inclusion and exclusion criteria

The target participants for this research will be undergraduate and postgraduate students from Universiti Tunku Abdul Rahman. The participants who fulfil the following criteria will be recruited for the interventional phase. 4 of 5 on the Migraine Screen Questionnaire, and 5 of 7 on International Classification of Headache Disorders 3rd edition (ICHD-3). Both genders aged between 18–40 years. The participants with a score of more than or equal to 5 on the visual aura rating scale, diagnosed to have a secondary headache (headache attributed to the causative disorder example: infection, trauma, or injury to head/ or neck) [28], pregnancy, took medication for neurological conditions like stroke, multiple sclerosis and took medications for cardiorespiratory conditions like asthma, took medications for headache and unwilling to participate will be excluded.

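### The aerobic target heart rate rests on two incompatible bases: a heart-rate-reserve formula with no intensity value, and a 64–76% range of maximum heart rate

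*Protocol article*

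**What the plan says.** The relevant text is in the protocol article under Aerobic training, in the paragraphs after Fig 5.

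- **The rule for calculation.** "the target heart rate will be calculated using the formula: [(max HR − resting HR) × %Intensity] + resting HR". This is the heart-rate-reserve method.
- **Its inputs.** "The maximum heart rate (max HR) will be calculated using the formula: 220-age", and "The resting heart rate (resting HR) will be calculated by measuring pulse at rest". The intensity term gets no number.
- **The range.** The same paragraph closes with "For moderate-intensity physical activity, the target heart rate should be between 64% and 76% of the maximum heart rate".
- **The use.** On the static bicycle, "the desired heart rate will be entered", and the display then shows whether the participant is inside, above or below the target range. On the treadmill, walking follows the target calculation, starts at a comfortable pace, and the speed is 4 mph, kept or raised to 5 mph according to perceived exertion.
- **The parallel control.** Borg's rating of perceived exertion (RPE) is to be kept at 11–14 on both machines.

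The Background gives the general aim: "For migraines, mild to moderate aerobic exercise is highly recommended".

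**The concern.** Two sentences in one paragraph both define the target heart rate, on different scales. A percentage of heart-rate reserve and the same percentage of maximum heart rate give the same number only when resting pulse is zero or the percentage is 100. If 64–76% of maximum is the target, neither the announced formula nor the resting-pulse measurement is needed to produce it. If the formula produces the target, the only percentages on the page belong to another scale.

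The number is used: someone has to enter a heart rate in the bicycle console. Exercise intensity is a central feature of the experimental arm, and the article says the trial will contribute an aerobic training protocol for people with migraine symptoms. A reader who wanted to repeat the training could not tell from this paragraph how the target was obtained.

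**Working it through.** **Inputs.**
- Maximum heart rate M = 220 − age (Aerobic training).
- Age 18–40 ("Both genders aged between 18–40 years", Inclusion and exclusion criteria), so M runs from 202 to 180.
- Percentages p = 0.64 and 0.76 (Aerobic training).
- Resting pulse R: not given. Assumed 60–80 beats/min, with 50–90 as a wider check.

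The article states no target in beats/min, so there is no figure to reproduce.

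**Step 1: the two readings.**
- A, share of maximum: A = p × M.
- B, the stated formula with the same p as its intensity: B = (M − R) × p + R.
- Difference: B − A = R × (1 − p). It does not depend on age.

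**Step 2: size of the difference (beats/min).**

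| Resting pulse | Lower limit (0.36 × R) | Upper limit (0.24 × R) |
|---|---|---|
| 50 | 18.0 | 12.0 |
| 60 | 21.6 | 14.4 |
| 70 | 25.2 | 16.8 |
| 80 | 28.8 | 19.2 |
| 90 | 32.4 | 21.6 |

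**Step 3: an example, age 20 and resting pulse 70 (M = 200).**
- A: 0.64 × 200 = 128 to 0.76 × 200 = 152.
- B: 130 × 0.64 + 70 = 153.2 to 130 × 0.76 + 70 = 168.8.

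The ranges do not meet.

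**Step 4: overlap in general.** The top of A minus the bottom of B is 0.12 × M − 0.36 × R.
- R = 70: 24.24 − 25.2 = −1.0 at age 18, and 21.6 − 25.2 = −3.6 at age 40. No overlap at any enrolled age.
- R = 60: 24.24 − 21.6 = 2.6 at age 18, and 21.6 − 21.6 = 0 at age 40.

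**Step 5: B as a share of maximum.** This is p + (1 − p) × R/M.
- Smallest lower end (R = 60, M = 202): 0.64 + 0.36 × 60/202 = 0.747.
- Largest upper end (R = 80, M = 180): 0.76 + 0.24 × 80/180 = 0.867.

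The upper end is above 0.76 for any resting pulse, so it is always above the article's own moderate range.

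**Step 6: the reverse conversion.** The formula intensity that reproduces A is (p × M − R)/(M − R).
- Over ages 18–40 and R = 60–80, the lower limit needs 0.352 to 0.488 and the upper limit 0.568 to 0.659.
- At R = 70 alone, going from age 18 to age 40 moves the lower limit from 0.449 to 0.411 and the upper from 0.633 to 0.607.

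So no single pair of intensity values turns the formula into 64–76% of maximum for everyone enrolled.

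**The case against.** The strongest reply is that only one of the two sentences yields a number. The formula gives none until an intensity is supplied, and the article nowhere says that 64–76% is that intensity. A reader might infer that the protocol states two numeric targets 14–29 beats/min apart; it does not. The gap appears only when percentages labelled as shares of maximum are entered in a formula for shares of reserve. One could also suppose that the range describes the moderate zone and that the formula's result is chosen to fall within it. Nothing excludes that reading, and step 6 shows it to be arithmetically possible: over the values considered, the largest lower equivalent (0.488) is below the smallest upper one (0.568). But the text does not say so, and it gives staff nothing with which to do it. This part of the objection makes the gap conditional; it does not remove the mismatch.

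Second, this is a condensed article, and Fig 4 is not shown. An intensity value may stand in the full protocol. That is fair, and the missing value is not counted here as a fault. The printed conflict of bases remains.

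Third, much else about the training is fixed: 40-minute sessions, three times a week for six weeks, pedalling at 50–60 rpm, walking at 4–5 mph and RPE 11–14. Treadmill speed is tied to RPE, and there are termination and safety rules. A reader might infer that the treatment is undefined, that participants will be driven too hard, or that uneven intensity will dilute the effect. The documents do not support these inferences. The other controls limit effort, the article gives no mapping from RPE to heart rate, and no calculation of dilution is available. This part stands, and it narrows the problem mainly to the heart rate entered on the bicycle.

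**Conclusion.** The point holds as an internal contradiction in a stated rule and should be fixed. The target heart rate is to be calculated on heart-rate reserve, while the only range supplied is on maximum heart rate.

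The size is conditional on two things: that 64–76% is used as the formula's intensity, and that resting pulse lies in the assumed range. Under those conditions the discrepancy is 14.4–28.8 beats/min at a resting pulse of 60–80 and 12.0–32.4 at 50–90. RPE does not settle which heart rate goes into the console.

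The contradiction does not touch randomisation, outcomes, sample size or analysis. It concerns one of several intensity controls in one arm of a pilot trial. Harm to participants and loss of effect are possible consequences, not demonstrated ones. No view is taken here on which intensity is right.

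**What to change.** Reconcile the two sentences in the Karvonen paragraph under Aerobic training:

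1. Let one basis, either share of reserve or share of maximum, set the target heart rate, and give the range on that basis.
2. Delete the other sentence or re-express it on the chosen basis.
3. Make the result consistent with the RPE 11–14 instruction, and say how the two relate on the bicycle when they disagree. The treadmill text already ties speed to RPE.

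The basis and the intensity are for the trial team to choose. The cost is a wording amendment and, if staff use a target-heart-rate worksheet, a matching correction to it. No further participants, visits or measurements are needed.

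### The aerobic target heart rate is set by a heart-rate-reserve formula with no intensity value, while the only percentages given are on the percent-of-maximum scale

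*Protocol article*

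**What the plan says.** All of this stands in the Protocol article, in the aerobic training text after Fig 5, except the age range, which is under Inclusion and exclusion criteria.

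- Method: "the target heart rate will be calculated using the formula: [(max HR − resting HR) × %Intensity] + resting HR". The article describes this as a method that "takes the resting heart rate into consideration by introducing the difference between maximum heart rate and resting heart rate".
- Inputs: "The maximum heart rate (max HR) will be calculated using the formula: 220-age", and "The resting heart rate (resting HR) will be calculated by measuring pulse at rest".
- Percentages: for moderate intensity, "the target heart rate should be between 64% and 76% of the maximum heart rate". No other percentage of heart rate appears, and none is assigned to the intensity term in the formula.
- Use: a desired heart rate is entered on the bicycle, and its display shows whether the participant is inside, above or below the target range. On the treadmill the heart-rate calculation comes before the walk, but speed follows perceived exertion: it starts at 4 mph and "depending on RPE response the speed will be either be maintained or increased to 5 mph". Borg exertion is to be kept at 11–14 on both machines.
- Population: "Both genders aged between 18–40 years".

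**The concern.** The formula and the percentages belong to different scales. Percent of heart-rate reserve depends on resting pulse; percent of maximum does not. The same percentage therefore means a different heart rate on each scale. The section neither converts one to the other nor says which governs.

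A trainer who follows the text has a formula with an empty slot and one pair of percentages. Putting the pair in the slot is a natural step, and it produces a target above the range that the article itself labels moderate. A trainer who treats the pair as the final target gets a lower range and makes no use of the resting pulse or the formula.

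At stake is the intensity delivered in the aerobic arm, how uniform it is across trainers and participants, and whether others can repeat it. This matters because, under Study goal and objective, the trial offers an aerobic protocol for migraine as one of its contributions.

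**Working it through.** **Inputs.** Maximum heart rate M = 220 − age, so M runs from 202 (age 18) to 180 (age 40). The percentages are p = 0.64 and 0.76. Resting heart rate R is measured for each participant and the article gives no figure, so R = 50, 60, 70 and 80 bpm are assumptions shown as a range. The article prints no bpm target or worked example, so there is no stated result to reproduce.

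**Formulas.**

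- Scale A, percent of maximum: p × M.
- Scale B, the reserve formula with the same p: p × (M − R) + R = p × M + (1 − p) × R.
- B minus A is (1 − p) × R: 0.36 × R at the lower limit and 0.24 × R at the upper.
- Overlap is the top of A minus the bottom of B: 0.76M − (0.64M + 0.36R) = 0.12M − 0.36R. It is positive only if R < M/3.

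**Worked case: age 20, R = 70 (assumed).** M = 200.

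- A: 0.64 × 200 = 128; 0.76 × 200 = 152.
- B: 0.64 × 130 + 70 = 153.2; 0.76 × 130 + 70 = 168.8.
- Shift: 0.36 × 70 = 25.2 bpm at the lower limit; 0.24 × 70 = 16.8 bpm at the upper.
- Overlap: none; the ranges are 153.2 − 152 = 1.2 bpm apart.

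**Across eligible ages (bpm).**

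| Age | M | A | B, R = 50 | B, R = 60 | B, R = 70 | B, R = 80 | Overlap at R = 50 / 60 / 70 / 80 |
|---|---|---|---|---|---|---|---|
| 18 | 202 | 129.3–153.5 | 147.3–165.5 | 150.9–167.9 | 154.5–170.3 | 158.1–172.7 | 6.2 / 2.6 / 0 / 0 |
| 20 | 200 | 128.0–152.0 | 146.0–164.0 | 149.6–166.4 | 153.2–168.8 | 156.8–171.2 | 6.0 / 2.4 / 0 / 0 |
| 30 | 190 | 121.6–144.4 | 139.6–156.4 | 143.2–158.8 | 146.8–161.2 | 150.4–163.6 | 4.8 / 1.2 / 0 / 0 |
| 40 | 180 | 115.2–136.8 | 133.2–148.8 | 136.8–151.2 | 140.4–153.6 | 144.0–156.0 | 3.6 / 0 (limits touch) / 0 / 0 |

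Overlap ends at R = M/3: 67.3 bpm at age 18, 66.7 at 20, 63.3 at 30 and 60.0 at 40. The largest overlap in the table, 6.2 bpm, is about a quarter of that person's range A (6.2 / 24.2 = 0.26).

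**The other reading.** Suppose 64–76% of maximum limits the formula's result. The intensity term must then be solved for as (p × M − R) / (M − R). At age 20 and R = 70 this is (128 − 70)/130 = 44.6% to (152 − 70)/130 = 63.1%. At age 40 and R = 70 it is (115.2 − 70)/110 = 41.1% to (136.8 − 70)/110 = 60.7%. The value changes with age and resting pulse, and the article gives no rule for it.

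**The case against.** The strongest reply is that the text never assigns 64–76% to the intensity term. Read literally, the percentages describe the target heart rate itself, so there is one range (128–152 bpm at age 20) and the higher one is the reader's construction. What is left would be a missing intensity value, which a condensed article might leave to the full protocol. The first half stands: a reader might infer that the protocol prescribes two contradictory ranges, and it does not say that. The second half does not dispose of the point. The article prints the formula as the way the target will be calculated, and on this reading the formula cannot be run as written.

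A second reply is that intensity has another control. Exertion of 11–14 applies on both machines, the treadmill speed responds to exertion rather than heart rate, and session length and frequency are fixed. This also stands in part. A reader might infer that the delivered dose is uninterpretable, or that both machines are driven by the disputed number; the text supports neither. The bicycle, however, is set by an entered heart rate, and the exertion band does not say which heart-rate range applies.

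A third reply is that the resting rates are assumed. They are, and at 50 bpm the ranges do share 3.6–6.2 bpm, so it would be wrong to say that they never overlap.

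The treadmill wording could also be read as a contradiction, because it provides for holding or raising speed but not for exertion above 14. The instruction to keep exertion within the band arguably covers that case, and the sections on termination and safety tell participants when to stop. It is a silence in the wording and a minor matter.

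**Conclusion.** The point holds. The section pairs a reserve formula that lacks an intensity value with percentages stated on the percent-of-maximum scale, and nothing in the article connects them. Using the only stated percentages in the stated formula raises the target by 0.36 and 0.24 times the resting rate at the two limits, which is 25.2 and 16.8 bpm at an assumed resting rate of 70. At that rate or above, the result lies wholly outside the range that the article calls moderate, for every eligible age. On the alternative reading the intensity term is undefined.

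The consequence is limited to the aerobic arm: the heart rate entered on the bicycle, and so the intensity delivered, can differ between trainers who each follow the text. The size rests on the assumed resting rates; the mismatch of scales does not. A reader might go on to infer that the randomised comparison loses its stated power or error control. Nothing here touches the sample size or error rates. Severity: should be fixed.

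**What to change.** Reconcile the two sentences so that the section states one intensity scale, the percentages that belong to it, and a worked example in bpm for a given age and resting pulse. If the reserve formula stays, its intensity term needs a stated value or range; if the percent-of-maximum range governs, the role of the formula needs to be stated. Which scale and range apply is for the sponsor to decide, and this review takes no view.

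As a minor matter in the same edit, make the treadmill speed wording consistent with keeping exertion at 11–14.

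The cost is a few lines in the protocol and in any trainer instructions, ideally before the first session. No change to sample size, outcomes or analysis follows.
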